### Organization

The primary investigator is responsible for the informed consent procedure, final patient selection, measurements, analysis and reports. The primary investigator will be assisted by a research assistant.

Data flow will be controlled by the primary investigator, using an administrative database system. Data-entry and control will be conducted by a research assistant under supervision of the investigator. The primary investigator is responsible for the data cleaning and analysis.

### Statistical analyses

All analyses will be performed according to the intention-to-treat principle. 95% confidence intervals will be calculated for the differences in percentages and means. Logistic regression will be used to analyze dichotomous variables, Poisson regression for the count-variables and linear regression for continuous variables. Ceiling and floor effects will be taken into account in the analysis of the questionnaires.

In order to test the independent contribution of the intervention on the outcome variables, multivariate regression analysis will be used to adjust for the possible confounders.

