### Feasibility of recruitment and sample size

Earlier studies have shown that 30% of the elderly hospital population is malnourished at admission [12-16]. For a clinically relevant difference of 20% in nutritional and functional status with a statistical significance level of 0.05 and a power of 80%, two groups of 80 patients were calculated to be sufficient.

A pilot study showed that inclusion of 140 malnourished patients per year is feasible. Taking into account an expected refusal rate of 30% at inclusion and loss to follow-up of 10% during the three months following discharge, we aim to include two groups of 100, to be reached in approximately two years.

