#### Fall-incidents

Patients will be asked to report all fall incidents weekly in a fall diary for a period of three months after discharge. A fall is defined as "an unintentional change in position resulting in coming to rest at a lower level or on the ground" [30].

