## Discussion

When designing the study protocol we had to make a number of considerations, which may lead to the following strengths and weaknesses:

Firstly, we have chosen a strict definition of malnutrition, because the most malnourished group is most likely to benefit from oral nutritional support. Since we have used the described cut-off points for malnutrition in previous studies as well, we expect that it is feasible to include a sufficient number of patients in the proposed study.

Secondly, we have chosen not to use strict exclusion criteria, but to include all eligible patients, even though they are suffering from a variety of (chronic) diseases. Their homogeneity stems from their age (>60y), degree of malnutrition (severe malnutrition) and background of disease (mainly non-surgical). We have performed earlier studies with this same group of relatively unselected patients with positive results of the nutritional intervention (after correcting for possible confounders such as age, sex, ethnicity, care complexity, disease etc) in comparison with usual care [11,34]. Moreover, if the results of a broad study like this one are positive, it justifies wide implementation, because the included group is representative for a mixed elderly hospital population; in contrast, selection of a more specific group would make the intervention less applicable to other patients groups.

Thirdly, for research purposes, standardized oral nutritional supplementation is chosen because simply advising patients to increase their intake by eating more has not proven to be a solution that can be relied on. From earlier studies, it is known that providing extra supplements does increase energy intake and leads to weight gain, in contrast to dietary advice alone (without extra supplements) [10,35-37].

Fourthly, the follow-up period of three months is chosen because this seems a reasonable recovery period after discharge in this particular patient group. Also, it is known that compliance of patients to take extra supplements diminishes after three months [38,39]. By making regular phone calls to the patients we try to maintain compliance.

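### Poisson regression is named for counts with no allowance for overdispersion; for falls, its 95% intervals would probably be too narrow (minor)

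*Protocol article*

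**What the plan says.** The protocol article assigns one model to each type of variable. Under Statistical analyses, after logistic regression for dichotomous outcomes, it gives "Poisson regression for the count-variables". The same section says that "multivariate regression analysis will be used to adjust for the possible confounders", and that "95% confidence intervals will be calculated for the differences in percentages and means". It does not mention dispersion, robust variance, observation time or a rate ratio.

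The count to which this applies is defined under Fall-incidents: "Patients will be asked to report all fall incidents weekly in a fall diary for a period of three months after discharge". Falls are thus a recurrent count, with the same planned diary period for everyone. The section on feasibility and sample size expects "loss to follow-up of 10% during the three months following discharge", so some diaries will be shorter than planned. The Discussion explains that strict exclusion criteria were avoided and that all eligible patients are included, "even though they are suffering from a variety of (chronic) diseases".

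The Design section lists falls neither as a primary outcome nor among the secondary outcomes.

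**The concern.** Ordinary Poisson regression takes the variance of the count to equal its mean. That holds only if patients with the same covariate values share one fall rate. This population is drawn from internal medicine, traumatology and vascular surgery wards and is deliberately left broad, so a common rate is improbable. When individual rates differ, the variance exceeds the mean, the model-based standard error is too small, and the interval for the treatment effect is too narrow. A chance difference in falls would then be declared significant more often than 5% of the time. The Background cites fewer falls as a benefit of supplementation in the community, so a falls result would be read as evidence.

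A separate matter is the time each patient was observed. If deaths or dropout shorten diaries more in one arm, a comparison of raw counts mixes the fall rate with time at risk.

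**Working it through.** **Inputs.** The protocol gives no fall rate, variance or interval width, so it has no figure of its own to reproduce here. Its 80 patients per group is for a 20% difference in nutritional and functional status and does not bear on falls. From the protocol: 100 per arm and 10% loss, giving 100 × (1 − 0.10) = 90 per arm. Assumed: mean falls per patient m and dispersion a, with negative binomial variance m + a·m².

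**Formulas.** The variance/mean ratio is φ = 1 + a·m. The Poisson standard error is too small by a factor √φ. Coverage of a nominal 95% interval is 2Φ(1.96/√φ) − 1. For φ = 2, 1.96/1.414 = 1.386, and coverage is 83.4%.

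**Results.** The last two columns are simulated type I error with no true effect: 8,000 trials per scenario, 90 patients per arm, 10% of them with a randomly shortened diary, log time as offset.

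| φ | m, a | √φ | Coverage | Plain Poisson | Robust variance |
|---|---|---|---|---|---|
| 1.0 | 0.2 to 1.0, 0 | 1.00 | 95.0% | 4.7–5.2% | 4.8–5.5% |
| 1.2 | 0.2, 1 | 1.10 | 92.6% | 7.1% | 5.5% |
| 1.5 | 0.5, 1 | 1.22 | 89.0% | 10.5% | 5.4% |
| 2.0 | 0.5, 2 | 1.41 | 83.4% | 16.0% | 5.7% |
| 3.0 | 0.5, 4 | 1.73 | 74.2% | 25.0% | 6.5% |

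The simulation agrees with the formula. Robust variance brings the error close to 5% and loses nothing when φ = 1.

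**Diary time and interval width.** With no overdispersion, 10% shortened diaries and no offset, simulated type I error was 4.5%, 5.1% and 5.6% for m = 0.2, 0.5 and 1.0. Shortened diaries alone do not materially narrow the interval.

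**Diary time and the estimate.** Without an offset, the expected ratio of counts is the rate ratio times the ratio of mean observed times. Suppose that patients who are lost contribute half the period on average. With 10% loss in each arm, mean time is 0.90 + 0.10 × 0.5 = 0.95 in both, and there is no bias. At the extreme, with all loss in one arm (20% against 0%), mean times are 0.80 + 0.20 × 0.5 = 0.90 and 1.00, and the count ratio is off by a factor of 0.90. Some imbalance is conceivable: the Background cites lower mortality with supplementation (relative risk 0.67), and only the intervention arm receives the six telephone consultations in Appendix 1.

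**The case against.** The strongest reply is that a journal article naming one model family per variable type does not exclude a scale parameter, robust standard errors or an offset, and that such details belong in the full protocol or analysis plan. Part of this stands: the silence on an offset is not an error in itself, and Poisson regression with robust variance is still Poisson regression. But the article does name a model, and a reader applying it as written would run the model-based version.

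Planned covariate adjustment will also absorb some heterogeneity. That stands too, and φ above should be read as the ratio left after adjustment. Adjustment removes only what measured covariates explain, and the baseline characteristics listed under Procedure do not name a history of falls.

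A reader might infer more than the protocol supports:

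- That falls in this trial are known to be overdispersed, so that the intervals will be too narrow. Nothing in the protocol gives a rate, a variance or a share of repeat fallers; overdispersion is likely, not established.
- That unequal diary time also narrows the intervals. The simulation shows that it does not; the offset concerns the estimate.
- That health care visit counts share the problem. Under Costs and Economic evaluation, visits are resource use valued into costs, and total costs are bootstrapped; no regression of visit counts is described.
- That the trial's main conclusions are at risk. The ICERs use functional status and ADL, with cost-utility ratios added, and the Background's remark on falls describes earlier work.

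**Conclusion.** The point holds as a minor, conditional one. Poisson regression is fixed for counts, falls are the one recurrent-event count listed as an outcome, and this mixed population makes overdispersion likely. If the residual variance/mean ratio lies between 1.2 and 3, model-based standard errors are too small by a factor of 1.10 to 1.73. If the ratio is 1, nothing is wrong. That range is an assumption, as are the negative binomial form and the fall rates behind the simulation. The consequence is confined to the falls comparison: the primary, named secondary and cost-effectiveness analyses stand as they are.

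**What to change.** Under Statistical analyses, qualify the rule for falls: negative binomial regression, or Poisson regression with robust standard errors, with the log of the diary time observed as offset, and the rate ratio reported with its 95% interval. Visit counts need no change.

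The cost is one line of text. No new data are needed beyond the weeks of diary completed, which the weekly diary can supply. Intervals for falls become wider by roughly √φ on the log scale: hardly at all without overdispersion, about 10% at a ratio of 1.2, and more if dispersion proves larger. That extra width is the correction itself. The change should be made before the falls data are analysed by arm.

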## Discussion

When designing the study protocol we had to make a number of considerations, which may lead to the following strengths and weaknesses:

Firstly, we have chosen a strict definition of malnutrition, because the most malnourished group is most likely to benefit from oral nutritional support. Since we have used the described cut-off points for malnutrition in previous studies as well, we expect that it is feasible to include a sufficient number of patients in the proposed study.

Secondly, we have chosen not to use strict exclusion criteria, but to include all eligible patients, even though they are suffering from a variety of (chronic) diseases. Their homogeneity stems from their age (>60y), degree of malnutrition (severe malnutrition) and background of disease (mainly non-surgical). We have performed earlier studies with this same group of relatively unselected patients with positive results of the nutritional intervention (after correcting for possible confounders such as age, sex, ethnicity, care complexity, disease etc) in comparison with usual care [11,34]. Moreover, if the results of a broad study like this one are positive, it justifies wide implementation, because the included group is representative for a mixed elderly hospital population; in contrast, selection of a more specific group would make the intervention less applicable to other patients groups.

Thirdly, for research purposes, standardized oral nutritional supplementation is chosen because simply advising patients to increase their intake by eating more has not proven to be a solution that can be relied on. From earlier studies, it is known that providing extra supplements does increase energy intake and leads to weight gain, in contrast to dietary advice alone (without extra supplements) [10,35-37].

Fourthly, the follow-up period of three months is chosen because this seems a reasonable recovery period after discharge in this particular patient group. Also, it is known that compliance of patients to take extra supplements diminishes after three months [38,39]. By making regular phone calls to the patients we try to maintain compliance.

Fifthly, care should be taken of in-hospital contamination between treatment groups. The majority of in-hospital patients will not be supplemented additional nutrition, either because they are not malnourished (± 70%) or because they are randomized to the control strategy (50% of the study population, 15% of the total population). Except for the primary investigator and research assistant, doctors and nurses will not be aware of the reason for not-supplementing. Thus we expect to be able to prevent contamination between treatment groups. In addition, hospital admission will last only 10 to 15 days and post-discharge treatment will be approximately three months. We expect that the post-discharge period to account for the majority of the effects. Contamination between treatment groups in not likely to occur after discharge.

Finally, this is the first prospective, randomized controlled trial evaluating whether transmural nutritional support is effective and cost-effectiveness when compared to usual care.

## Conclusion

In this study we will evaluate in a randomized controlled trial whether transmural nutritional support, compared to usual care, is effective and cost-effective, in malnourished elderly patients. We will determine changes in activities of daily living, physical activity, functional limitations, body weight, body composition, quality of life, and muscle strength between the intervention and control group during the period between admission to hospital and three months after discharge.

## Appendix 1

Standardised transmural nutritional support in the intervention group:

- Energy and protein enriched diet (in-hospital period)

- Two additional servings of an oral nutritional supplement, leading to an expected increase in intake of ± 600 kcal/day and 24 g protein/day per day (entire study period)

- 400 IE vitamin D3 and 500 mg calcium (Calci Chew-D3, Sandoz) per day (entire study period)

- Six consultations by telephone by a dietitian in order to give advice and to stimulate compliance to the proposed nutritional intake (every other week after discharge from the hospital)
